### Experimental group

Patients in the experimental group will be given HuoXueSanFeng acupuncture therapy, in addition to the control group interventions. To ensure the optimal effects of acupuncture stimulation, all the therapists are required to have clinical experience of acupuncture treatments for at least 8 years.

Disposable, sterile needles with a diameter of 0.25 mm and a body length of 40 mm (HUATO, Suzhou, China) will be used. Patients are asked to adopt the supine position. Acupoints used here are bilateral *Renying* (ST9), *Hegu* (LI4), *Quchi* (LI11), *Taichong* (LR3), and *Zusanli* (ST36). The acupoint locations with reference to the World Health Organization (WHO) standards in the Western Pacific Region, and the corresponding manipulations of the aforementioned acupoints are listed in Table 3, which accord with those described in a previous paper [32]. All the manipulations will be applied for 1 min and the needles are retained for 30 min.

**Table 3 Tab3:** Acupoint form

Treatment methods	Points	Location	Acupuncture method
Acupuncture method of *HuoXueSanFeng*	*Renying* (ST9)	In the neck next to the thyroid cartilage, the anterior border of sternocleidomastoid, at the common carotid artery pulsation site	Using the twisting technique of the reinforcing method of the second definition from [name] academician, namely low amplitude (torsional amplitude less than 90°), high-frequency (120–160 times/min), the operation lasting for 1 min
	*Hegu* (LI4)	In the back of the hand, between the first and second metacarpals, at the midpoint of the second metacarpal radially	Using the twisting technique of the first definition of the reducing method from [name], academician
	*Taichong* (LR3)	In the dorsum of the foot, at the head of the first metatarsal space	Using the twisting technique of the first definition of the reducing method from [name], academician
	*Quchi* (LI11)	In the lateral end of the cubital crease, at the midpoint of the ligature between the end point of the cubital crease and the lateral epicondyle of the humerus with the elbow bent	Using the twisting technique of the first definition of the reinforcing method from [name], academician
	*Zusanli* (ST36)	In the anterior lateral of crus, 3 B-cun under *Dubi* (ST35), one transverse finger width from the anterior tibial border	Using the twisting technique of the first definition of the reinforcing method from [name], academician
Acupuncture method of *XingNaoKaiQiao*	*Neiguan* (PC6)	In the volar aspect of the forearm, at the junction of *Quze* (PC 3) and *Daling* (PC7), 2 B-cun above the wrist crease in the space between tendon palmaris longus and vagina tendinis musculi flexoris carpi radialis	Using the combination of the reducing method of twirling lifting and thrusting needles, the operation lasts for 1–3 mins
	*Shuigou* (DU26)	In the face, at the intersection point of the upper 1/3 and middle 1/3 of the philtrum groove	Using the reducing method of “sparrow-pecking” until tears fall or appear in the eyes
	*Sanyinjiao* (SP6)	In crus inside, 3 B-cun above the upper border of the medial malleolus of the ankle at the posterior border of the tibia	Using the reinforcing method of twirling, lifting, and thrusting needles, until the lower limb consecutively twitches 3 times
	*Jiquan* (HT1)	At the apex of the axilla, the site of the pulse of the axillary artery	Using the reducing method of twirling, lifting, and thrusting needles, until the upper extremity twitches 3 times
	*Chize* (LU5)	In the cubital crease, at the depression of the bicipital muscle tendon radialis at the elbow	Using the reducing method of twirling, lifting, and thrusting needles, until the needling feeling is felt from the elbow joint to the fingers; or manual extorsion 3 times
	*Weizhong* (BL40)	At the midpoint of the popliteal crease, at the midpoint between the femoral biceps tendon and the semitendinosus tendon	Using the reducing method of twirling, lifting, and thrusting needles, until the lower extremity twitches 3 times

B-cun: proportional bone cun. This method divides the height of the human body into 75 equal units. Using joints on the surface of the body as the primary landmarks, the length and width of every bodily region is measured by such proportions

The patients will be provided with *HuoXueSanFeng* acupuncture treatments six times per week in the first 6 weeks, referred to as the consistent treatment period. The consolidation period consists of three sessions of *HuoXueSanFeng* acupuncture treatments weekly in the following 6 weeks with a total of 12 weeks of *HuoXueSanFeng* acupuncture treatments performed in the experimental group.

### Control group

The control group will receive one antihypertensive medication on the basis of ischemic stroke routine care. In our trial, basic ischemic stroke medical care includes 12 weeks of *XingNaoKaiQiao* needling therapy plus other forms of routine stroke care. Twelve weeks of *XingNaoKaiQiao* needling therapy should also aid in the improvement of compliance in both groups for its high acceptance and remarkable effectiveness for stroke. All medications must be recorded in the drug combination form, including the types, dosage, usage frequency and time, etc., in order to provide data for analysis and the report summary. The acupuncture needle is the same with that used in *HuoXueSanFeng* acupuncture treatments. The acupoint locations and manipulations are presented in Table 3. No common acupoints are used in the two formulas. The retention time and frequency of treatments are identical to *HuoXueSanFen*g acupuncture therapy. During the entire process of our study, the control-group patients are prohibited from receiving any BP-lowering acupuncture therapy, and any violations will be recorded.

### Antihypertensive medication adjustment

After randomization, an electronic BP machine and a BP diary notebook will be delivered to all patients for measuring and recording their BP levels. During the first 6-week inpatient treatments, they will be instructed how to use the machine accurately. BP will be measured within 1 h after morning waking before taking antihypertensive medications, at 3 h after taking antihypertensive medications, at 4 p.m. and before bedtime over the entire process. On each occasion, three repeated measurements of supine BP, following a rest of at least 15 min, will be conducted at 1-min intervals. The antihypertensive medication classes in both groups will be recorded. Lifestyle advice regarding hypertension and stroke will be given to the patients. In the experimental group, if the patients have a mean BP level below 140/90 mmHg for three consistent days, they will receive solely acupuncture treatment; thereafter, once their BP levels increase to ≥ 140 mmHg systolic and/or ≥ 90 mmHg diastolic for 1 month, prior antihypertensive medications should be re-dispensed. Otherwise, if BP levels are ≥ 160 mmHg systolic and/or ≥ 100 mmHg diastolic for three consistent days after initiating *HuoXueSanFeng* acupuncture treatments or over the follow-up period, additional antihypertensives should be prescribed. All the medication adjustments will be filled out in the Case Report Forms (CRFs).

For the control group, when the average systolic BP increases to ≥ 160 mmHg and/or diastolic BP ≥ 100 mmHg lasting for three continuous days in the study period, other antihypertensive drugs will be prescribed in the opinion of the treating physicians, and these will be documented for final analyses.

### Outcome assessments

The assessors are blinded to grouping. The primary outcome will be all cases of recurrent stroke over a follow-up period of 9 months after receiving 12-week acupuncture treatments. Secondary endpoints, such as 24-h ambulatory BP, TCM syndrome score, Short Form 36-item Health Survey (SF-36) results, National Institute of Health Stroke Scale (NIHSS) and Barthel Index (BI) scale scores will be assessed at baseline, 6 weeks, and 12 weeks post initiating treatments; serum nitric oxide (NO), endothelin (ET), homocysteine (Hcy), soluble CD40 ligand (sCD40L), and copeptin levels and cardiac ultrasound, carotid artery ultrasound, transcranial Doppler, and lower extremity ultrasound results will be evaluated at baseline and 12 weeks after treatment. Other safety indicators including baseline general physical examination, blood, urine, and stool routine tests, coagulation function, D-dimer level, liver and kidney function, electrocardiograph as well as a chest X-ray will also be examined 12 weeks after randomization. At 6 months after randomization, blood, urine, and stool routine tests, coagulation function, D-dimer level, liver and kidney function, electrocardiograph, NO, ET, Hcy, sCD40L, and copeptin tests will be re-checked, with some hope of improving patients’ adherence to treatment. All-cause mortality will also be evaluated during the follow-up period. The Essen Stroke Risk Score (ESRS) will be additionally assessed at baseline and 1 year post randomization.

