**Methods:**

This is a large-scale, multicenter, subject-, assessor- and analyst-blinded, pragmatic RCT. A total of 480 patients with hypertension and ischemic stroke will be randomly assigned to two groups: an experimental group and a control group. The experimental group will receive “*HuoXueSanFeng*” acupuncture combined with one antihypertensive medication in addition to routine ischemic stroke treatment. The control group will only receive one antihypertensive medication and basic treatments for ischemic stroke. *HuoXueSanFeng* acupuncture will be given for six sessions weekly for the first 6 weeks and three times weekly for the next 6 weeks. A 9-month follow-up will, thereafter, be conducted. Antihypertensive medication will be adjusted based on BP levels. The primary outcome will be the recurrence of stroke. The secondary outcomes including 24-h ambulatory BP, the TCM syndrome score, the Short Form 36-item Health Survey (SF-36), the National Institute of Health Stroke Scale (NIHSS), as well as the Barthel Index (BI) scale will be assessed at baseline, 6 weeks and 12 weeks post initiating treatments; cardiac ultrasound, carotid artery ultrasound, transcranial Doppler, and lower extremity ultrasound will be evaluated at baseline and 12 weeks after treatment. The safety of acupuncture will also be assessed.

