The synergistic BP-lowering effectiveness of acupuncture and antihypertensive agents has been proven, despite there formerly being insufficient evidence for acupuncture alone in lowering BP [22]. Recently, researchers have reported some positive results regarding sole acupuncture treatment for hypertension [23–25]. The reasons for this paradoxical situation could be disparities in acupuncture manipulation skills as well as other technical factors. Considering the limited reporting quality, the effect of pure acupuncture in lowering BP remains elusive.

Given that complementary and alternative interventions are recommended for mild and moderate hypertensive patients [26], we cautiously decided to select the hypertensive patients with uncontrolled BP (systolic BP ≥ 140 and < 160, or/and diastolic BP ≥ 90 and < 100 mmHg) who were taking one class of antihypertensive drugs to be the participants. The difference between the control and experimental groups is that in our experimental group, after a period of BP-lowering acupuncture add-on treatment, i.e., the “*HuoXueSanFeng*” needling method which has been proved to positively treat primary hypertension [27–33], if the BP falls below 140/90 mmHg, the prior antihypertensive drugs will be ceased, so as to observe the clinical effects of pure acupuncture on BP. Moreover, aiming to create a situation that is analogous to the real world, antihypertensive drugs will be adjusted based on the patients’ BP readings (detailed in the “Antihypertensive medication adjustment” section below) in both groups, respectively.

Altogether, our team conceived this high-quality, pragmatic randomized controlled clinical trial with the primary objective to determine whether BP-lowering acupuncture add-on therapy could decrease the recurrence of first-time ischemic stroke in patients during the 9-month follow-up period.

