## Methods/design

### Study design and setting

Our study is a prospective, multicenter, subject-, assessor-, and analyst-blinded, pragmatic randomized controlled trial. The research period lasts from May 2015 to May 2020 (201507001-08). Five centers from five cities will be involved in recruitments, treatments, and assessments. Informed consent will be obtained after screening for eligibility, then baseline assessments will be conducted before randomization (details in Table 1). Eligible patients will be allocated, in a 1:1 ratio using a dynamic randomization procedure, into a BP-lowering acupuncture therapy group (experimental group) and a control group. After randomization, the patients in the experimental group will be additionally treated by the *HuoXueSanFeng* needling method (a BP-lowering regimen) plus the “*XingNaoKaiQiao*” needling method [34] (a formula for stroke) over 12 weeks, whereas the control group will be only given the *XingNaoKaiQiao* needling method for 12 weeks. Other routine ischemic stroke treatments in both groups will be provided. During the whole process of our study, the antihypertensive medications will be adjusted based on the BP level in the two groups (details displayed in the “Antihypertensive medication adjustment” section). The primary outcome will be all recurrent stroke cases over a follow-up period of 9 months after receiving 12-week acupuncture treatments. Our protocol presentation is in accordance with the Standard Protocol Items: Recommendations for Interventional Trials 2013 (SPIRIT 2013) guidelines. The study flowchart is presented as Fig. 1.

**Table 1 Tab1:** Study schedule

Period	Screening	Baseline	Treatment (weeks 1–12)		Follow-up (weeks 13–48)	
Week	Week 0	Week 0	Week 6	Week 12	Week 24	Week 48
Eligibility	×					
Demographic medical history	×					
Informed consent		×				
Basic laboratory test®	×			×	×	
24-h ABPM		×	×	×		
TCM syndrome score, SF-36		×	×	×		
NIHSS, BI		×	×	×		
ESRS		×				×
Follow-up BP					×	×
Recurrence of stroke						×
NO, ET, Hcy, sCD40L, Copeptin		×		×	×	
ECG		×		×	×	
Chest X-ray		×				
Color Doppler ultrasound®		×		×		
All-cause mortality rate						×
Combined diseases and drugs	Record at any time					
Antihypertensive medication adjustment	Record at any time					
Adverse event	Record at any time					
Daily BP	Record everyday (based on BP diary)					
Safety of acupuncture	Record at any time					
Patients’ compliance				×		

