### Follow-up

After finishing the acupuncture treatments, patients will be followed up monthly via telephone for 1 year post randomization. Stroke recurrence, all-cause deaths and BP control will be investigated and recorded in the CRFs. The patients will be required to use the BP diaries to record their BP four times daily. If the BP is ≤ 160 mmHg systolic and/or ≤ 100 mmHg diastolic for 1 month, the patient will be advised to take antihypertensive medications, which will be documented in the CRF.

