### Sample size and statistical methods

The sample size calculation of the study was based on China’s Ministry of Health data suggesting that at least 197 patients are required in each group for the final analysis to achieve a power of 80% to demonstrate a recurrence rate of 7%, rather than 16% resulting from *HuoXueSanFeng* acupuncture (data not shown, please see Additional file 1), at a two-sided significance level of 5%. Given a projected dropout rate of 15%, we aimed to recruit 480 patients for the study.

Statistical analysis will be conducted by a third party who is unaware of the treatment allocation. Data will be analyzed with SAS 9.1 and SPSS 19.0 software packages. Two-sided *P* < 0.05 represents statistical significance for all the analyses. Both intention-to-treat analysis (ITT) and per-protocol (PP) analysis will be performed. We will compare the result of ITT analysis with that of PP analysis to determine whether the results are consistent. For the ITT analysis, missing data will be handled by Last Observation Carry Forward rules, in brief, the finally observed data will be used for replacement of the missing primary variables.

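### As worded, the primary outcome and all-cause mortality are counted only after the 12-week treatment, so recurrences and deaths in weeks 1–12 after randomisation fall outside both endpoints

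*Protocol article*

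**What the plan says.** The Outcome assessments section states: "The primary outcome will be all cases of recurrent stroke over a follow-up period of 9 months after receiving 12-week acupuncture treatments". Study design and setting says the same: "The primary outcome will be all recurrent stroke cases over a follow-up period of 9 months after receiving 12-week acupuncture treatments". The primary objective at the end of the Background asks whether the add-on treatment "could decrease the recurrence of first-time ischemic stroke in patients during the 9-month follow-up period". The abstract places that period after the 12 weeks of acupuncture: "A 9-month follow-up will, thereafter, be conducted".

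Table 1 heads the period "Follow-up (weeks 13–48") and ticks recurrence of stroke and all-cause mortality once each, at Week 48. On deaths, Outcome assessments says: "All-cause mortality will also be evaluated during the follow-up period". Under Follow-up, once acupuncture has finished, "patients will be followed up monthly via telephone for 1 year post randomization", and recurrence and deaths are recorded in those calls.

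Study design and setting puts randomisation before the 12 weeks of treatment. The sample size aims "to achieve a power of 80% to demonstrate a recurrence rate of 7%, rather than 16" per cent, with no period attached to either rate. The same section promises intention-to-treat and per-protocol analyses.

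**The concern.** A randomised comparison is protected from selection only if events are counted from randomisation in everyone randomised. Here counting starts 12 weeks later. Patients enter 2 to 6 weeks after the index stroke, so the window opens about 14 to 18 weeks after it.

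The excluded weeks are not a neutral run-in. Every acupuncture session falls in them: 6 × 6 + 3 × 6 = 54 for a patient who completes the schedule. The antihypertensive adjustment rules also differ between arms from the start, because only the experimental arm has a rule for stopping the prior drug when blood pressure falls. If the experimental strategy prevented or provoked strokes in this period, the primary result would not show it. If the arms differed early, the later comparison would be between groups already altered by what happened after randomisation. All-cause mortality has the same gap.

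**Working it through.** **1. Where the window starts.** Four places agree that it starts after treatment: the primary objective, Study design and setting, Outcome assessments, and the abstract's sequence. Table 1 (weeks 13–48) and the start of the telephone calls fit this. Nowhere does the article say that a stroke in weeks 1–12 counts as a primary event.

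**2. Share of time left out.** 12/52 = 23% of a year from randomisation, or 12/48 = 25% on Table 1's weeks.

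**3. The plan's own sample size.** Inputs from Sample size and statistical methods: p1 = 0.16, p2 = 0.07, two-sided 5%, power 80%. With mean p = 0.115 and pooled variance under the null:

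n = [1.960 × √(2 × 0.115 × 0.885) + 0.8416 × √(0.16 × 0.84 + 0.07 × 0.93)]² / 0.09²
= (1.960 × 0.4512 + 0.8416 × 0.4467)² / 0.0081 = 196.06, so 197.

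This reproduces the stated figure. Power is 80.2% at 197 per arm and 81.5% at 204 per arm (480 × 0.85 / 2 = 204).

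**4. What the window could do to power.** The article gives no period for 16% and 7%, so this step is conditional. *Assumption: both are one-year rates with a constant hazard.* The risk over w weeks for a patient still stroke-free at week 12 is 1 − (1 − p)^(w/52).

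| Window | Control | Experimental | Power at 197 | Power at 204 |
|---|---|---|---|---|
| 40 weeks (52 − 12) | 12.6% | 5.4% | 69.7% | 71.2% |
| 39 weeks (9 calendar months) | 12.3% | 5.3% | 68.6% | 70.1% |
| 36 weeks (weeks 13–48) | 11.4% | 4.9% | 65.2% | 66.8% |

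If every randomised patient stays in the denominator, early strokes are not counted and the close is week 52, the rates are 16% − 3.9% = 12.1% and 7% − 1.7% = 5.3%. Power is then 66% at 197 and 67% at 204, inside the same range.

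*Alternative assumption: 16% and 7% already describe the 9-month window.* Power stays at 80%. The problem in step 1 is unchanged.

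**5. Events outside the window, on the one-year assumption.** Control: 240 × (1 − 0.84^(12/52)) = 240 × 0.0394 = 9.5. Experimental: 240 × (1 − 0.93^(12/52)) = 240 × 0.0166 = 4.0. Recurrence may not be constant over the first months after a stroke, and the article gives no figure for its shape.

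**6. Where the window ends.** Table 1 puts the Essen Stroke Risk Score at Week 48, and Outcome assessments puts it at one year after randomisation. The laboratory re-check is at Week 24 in Table 1 and at 6 months in the text. With 4-week months, 12 weeks + 9 × 4 weeks = week 48, which is also 12 months. The labels therefore appear to name one visit.

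**The case against.** **Early strokes will be seen.** Table 1 records adverse events and combined diseases at any time, and serious adverse events go at once to the project leader and the Ethics Committee. This stands as far as recording goes. It does not put such strokes into the primary count, but it does make the correction cheap.

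**The Week 48 tick may be cumulative.** The abstract names the outcome simply as recurrence of stroke, and one tick at the end would suit a count from randomisation. The table does not say so, and the objective and both definitions say otherwise.

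**The scoring of an early stroke is not stated.** A reader might infer that such a patient is scored as event-free or is removed from the analysis. The article says neither. Its last-observation rule for missing primary data could even carry an early stroke forward as an event. What can be said is that the definition leaves these strokes out and that their handling is unclear.

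**The closing dates conflict.** A reader might infer this from 9 months, Week 48 and one year. The paired visits in step 6 point to a 4-week-month convention, so this is mostly loose labelling.

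**A durable effect may be what was intended.** That is a legitimate question and can be kept as a secondary analysis. Table 2 states the aim as efficacy on stroke recurrence, without limiting it to late recurrence.

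**Conclusion.** The point holds on the start of the window. As worded, the primary outcome and all-cause mortality omit the first 12 weeks after randomisation, 23–25% of the observation time, when all the acupuncture is given and the arms' antihypertensive rules already differ. The primary comparison does not run from randomisation, and this undermines the intention-to-treat analysis that the article promises. This conclusion rests on the text alone and needs no assumption about event rates.

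Three stronger readings are not supported:

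- The sample size is not wrong. A fall in power to roughly 65–71% follows only if 16% and 7% are one-year rates with a constant hazard, and the article does not give their time base.
- Death is not part of the primary outcome. Early deaths are missing from the separate mortality endpoint, and they also reduce the number of patients at risk when the primary window opens.
- The final date is inconsistently labelled rather than shown to be in real conflict.

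**What to change.** - Define the primary outcome as any recurrent stroke, fatal or non-fatal, from randomisation to one fixed date, in all randomised patients.
- Count all-cause death over the same period.
- Keep the 9-month post-treatment window as a secondary landmark analysis, labelled as such.
- Use one label for the final date in the objective, Tables 1 and 2, Outcome assessments and Follow-up.
- Show in Table 1 that recurrence and death are recorded from randomisation onwards.
- State the period to which 16% and 7% refer. If it differs from the redefined outcome period, recompute the sample size.

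The cost is a protocol amendment and a line on the case report form. No new visit is needed, because patients attend six times weekly for the first 6 weeks and three times weekly for the next 6, and the monthly calls already cover the rest. No treatment rule changes.
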